## Abstract

**Background:**

Dating violence has an alarming prevalence among Brazilian adolescents. School-based preventive programs have been implemented, but remain isolated initiatives with low reach. Health communication strategies based on innovative technologies with a high potential of diffusion are urgent. This study aimed to develop a computer-tailored intervention to prevent victimization and perpetration of dating violence among Brazilian youth.

**Methods:**

The intervention, called Dating SOS (SOS Namoro), is based on the I-Change Model and attachment theory and is a comprehensive preventive program targeted to young people with a current partner. The intervention design included the stages of needs assessment; definition of objectives of change; development of the library of messages; elaboration of a questionnaire for tailoring feedbacks according to the relevant variables; integration of the content in the software Tailor Builder; pre-testing; and usability and efficacy evaluation planning. Dating SOS is composed of four online sessions. The first session gives a tailored orientation on attachment style and risk perception of violence. The second session addresses knowledge on conflict management, positive and negative social models of intimate relationships and an action plan to improve everyday interactions. The third session covers social norms, self-efficacy and an action plan to cope with conflicts. The fourth session discusses attitudes, social support and an action plan to protect from violence. Improvements on the interface and tailoring refinement was done after pre-testing to improve attractiveness and decrease risk of iatrogenic effects.

**Discussion:**

The principal merit of the present study resides in the development of an innovative strategy based on the qualified use of the internet for education surrounding romantic relationships and the prevention of dating violence among adolescent and young Brazilians, a hitherto unaddressed need in the field. The intervention usability and efficacy should be investigated in further studies.

**Trial registration:**

Brazilian Registry of Clinical Trials. RBR-9frj8q. Prospectively registered on July 25, 2019. http://www.ensaiosclinicos.gov.br/rg/RBR-9frj8q/

## Background

Violence received from and practiced against a romantic partner is widespread among Brazilian adolescents. Evidence shows that eight of every ten adolescents (age 15 to 19) have already been victims of or have practiced some type of aggression against an intimate partner at some point in their lives, particularly of a sexual or emotional nature [1]. The predominant constructs of femininity and masculinity contribute to the normalization of dating violence and make its recognition difficult among Brazilian adolescents, as violent manifestations are taken as expressions of love or playfulness inherent to intimacy [2, 3]. This violence invisibility impedes help-seeking and sustains victimization and perpetration of violence by intimate partners in adolescence. Findings of a national study show that adolescents rarely seek help when they are victims of their intimate partner, but when they do so, they prioritize friends and family as the sources while professional help is sought less often [4].

Effective prevention and early intervention services aimed at this type of violence in the adolescent public [5] as well as studies with these purposes are lacking. Results of an evaluation of the implementation quality a law aimed at the eradication, prevention, and punishment of domestic violence against women (the Maria da Penha Law), reveal that educational actions focused on prevention of violence in adolescents, boys or girls, are rare [6]. The paucity of preventive services identified in public policies is also reflected in research. As opposed to other countries in the Americas, which produce frequent research on the prevention of dating violence among adolescents, there is a scarcity of evidence-based prevention interventions in Brazil [7].

Recent Brazilian interventions against partner violence are offered face-to-face in the school environment and conducted in a workshop format by previously trained facilitators [8–12]. Evidences has pointed reduction in sexist and homophobic beliefs [8] and dating violence perpetration [10], increasing in emotion regulation skills [9], and intervention’s acceptability [11, 12]. Even with their promising results, such interventions require institutional support, space in the school’s curriculum schedule, and qualified personnel for their execution in new contexts, all of which hinder their diffusion at a national level resulting in limited public health impact.

An alternative mode of intervention that that may be easier to disseminate and adopted can be computer-tailored intervention (CTI). A CTI consists of the adaptation of health education material to one specific person after an individualized evaluation by an algorithmic process to generate customized feedback and guidance for the user [13]. As in traditional clinical counseling, individual evaluations are followed by feedback and guidance tailored to the participants’ beliefs, behaviors, and needs. However, in contrast to the traditional clinical approach, such feedback and tailored guidance is offered through printed letters, email, mobile phones, and other mobile devices instead of the face-to-face mediation of a professional.

CTI differs from general internet intervention modes (eHealth) that do not use tailored guidance derived from individual evaluations (commonly called computer-based interventions or internet-based interventions) [14]. Several studies of communication in health care reveal consistent evidence that tailored messages, when compared to general messages, tend to be read more often and are remembered and considered more relevant and appealing [15, 16]. Therefore, tailored interventions are more effective and efficient as a health education strategy than other means of general mass communication. Additionally, CTI seems to be highly appropriate for adolescents who are more accustomed to technology than older generations.

While the application of tailored internet-mediated interventions to promote positive health habits is broad [17, 18], their application in the prevention of dating violence is still limited and recent. The first study focusing on this in the literature was conducted by Levesque, Johnson and Prochaska [19], who developed an intervention called *Teen Choices*, based on the transtheoretical model, which sought to prevent dating violence and foster healthy relationships in adolescence. The intervention, composed of a single session, contains different guidance for participants not dating, dating with a low risk of violence, and dating with a high risk of violence. The feedback is tailored according to readiness to engage in healthy relationships and in the seeking and offering of help. The results showed that the *Teen Choices* participants, compared to the control group, presented a significant reduction in perpetration and victimization of physical and emotional violence at 6 and 12 months [20]. The results were more expressive in those who presented a prior history of violence in intimate relationships.

In Brazil, the use of information and communication technologies for mental health promotion is rare [21] and studies using CTI are still embryonic [22] and generally address the reduction of addictive behaviors, such as smoking [23]. Given this situation, the current study innovates by developing an intervention to prevent dating violence among Brazilian adolescents. The intervention, called SOS Namoro (hereafter Dating SOS), was designed to reduce victimization and perpetration of dating violence and increase relationship quality, conflict management skills, and help seeking. It is a universal prevention strategy, targeting youths between 15 and 29, who have an affective-sexual partner at the beginning of the intervention, regardless of being in violent relationship or being exposed to dating violence risk factors. It is based on two theoretical models: the integrated change model, also known as the I-Change Model, and attachment theory.

### Theoretical basis

The I-Change Model [24, 25] is a composite of several models and socio-cognitive theories, including Azjen’s theory of planned behavior [26], Bandura’s social cognitive theory [27], Prochaska’s transtheoretical model [28], Janz and Becker’s health beliefs model [29], and goal setting theories [30]. According to the model (see Fig. 1), behavior and behavior change is a process of several phases and each phase is determined by different types of factors.

**Fig. 1 Fig1:**
[figure not shown]
Integrated Change Model (Source: De Vries H. An integrated approach for understanding health behavior; the I-Change Model as an example. Psychol and Behav Sci Intern Journal, 2017;2(2). DOI:10.19080/PBSIJ.2017.02.555585)

First of all, a person needs to become aware of the problem, which is determined by awareness of his/her own behavior (i.e. is the behavior that I am doing appropriate, am I behaving in a violent way), knowledge (i.e. what are considered to be sexually violent behaviors?); risk perceptions (i.e. am I at risk of violating someone and what are the consequences); and perceived cues (i.e. what are the situations that may prompt me to become sexually violent). Second, when a person becomes aware of a problem and its own role in the problem, he/she may become open to become motivated to change unhealthy behavior. Factors that are important here are: attitudes towards the behavior and the perceived pros and cons of it (e.g. when I am sexually violent I can show that I am in charge of things), the perceived social support (e.g. my mates think it is okay to be sexually violent), and self-efficacy (e.g. when I feel stressed I find it difficult to control myself and not become sexually violent). The combination of positive attitudes, supportive norms and high self-efficacy will lead to a positive intention to perform a healthy behavior. Third, a positive intention does not automatically translate into the desired goal behavior but requires action planning (e.g. what will I do when I feel stressed), actual realization of these plans, the skills, and sometimes the removal of certain barriers.

Lastly, the I-Change Model postulates that these factors are influenced by a wide array of predisposing factors, such as psychological, behavioral, socio-environmental factors. Additionnaly, the model postulates that awareness, motivation and action can be influenced by developing communicative actions, of which the effects are determined by personal factors (e.g. level of education), message factors (e.g. clearly written with clear instructions, tailored to a specific person), source factors (e.g. using peers that provide information), and channel factors (e.g. the choice for interpersonal, personal or eHealth channels).

Dating SOS will operate through three mechanisms outlined by the I-Change Model. The first mechanism consists in raising awareness of dating violence as a problem by promoting knowledge of the phenomenon and its impact on health. The second comprises strengthening motivation to protect oneself against violence from an intimate partner by increasing attitudes favorable to the non-violent management of conflicts and unfavorable to the acceptance of violence, enhancing critical thinking about pro-violence social norms, aiding in the identification of healthy models of loving relationships and sources of social support when facing violence, and developing self-efficacy to deepen emotional intimacy in the relationship and reduce the use and acceptance of violent conflict resolution strategies. The third covers fostering self-protective intentions by means of developing clear action plans for facilitating day-to-day communication with the partner, managing conflicts without violence, and protecting oneself should violence arise (for example, seeking help). Applications of the I-Change Model to study and intervene on violence, showed the importance of these determinants [31], as well as the efficacy of intervening on these determinants to reduce violence successfully [32, 33].

In addition to the I-Change Model, attachment theory was adopted as a secondary theoretical basis for Dating SOS [34]. Although this theory has been extensively used to explain how attachment may explain the process leading to intimate partner violence [35] and prevention to dating violence [36], its use in CTI to this end has not yet been recorded. The choice of attachment theory to base Dating SOS upon resides in the evidence that adolescents with insecure affective bonding styles tend to use more destructive conflict management strategies and are more frequently victims of dating violence than those securely attached [37, 38]. Evidence from a study of a Brazilian sample with couples in various stages of romantic relationships corroborates these findings [39].

Insecure attachment styles stem from rejective, inconsistent, intrusive, or abusive parenting practices that foment the development of internal working models characterized by distrust and insecurity in the establishment of loving bonds as well as an image of themselves as undeserving of love [40, 41]. In turn, secure attachment style results from parental care responsive to the needs of the child who, as a consequence, develops lifelong internal working models predictive of a positive image of oneself and one’s partner, facilitating the building of intimate relationships in adulthood and increasing the likelihood that they be longer-lived, healthier, and more secure. In this way, romantic love in adolescence and adulthood can be understood as an attachment process stemming from the first attachment experiences in childhood.

Low levels of anxiety and avoidance in affective relationships characterize secure attachment style, whereas insecure attachment styles present elevated levels of anxiety and/or avoidance [42]. Avoidance is related to the degree of comfort individuals experience in the face of emotional closeness and intimacy. Applied to romantic relationships, highly-avoidant individuals are reluctant to establish intimate relationships and seek emotional comfort based on the concept that intimacy is threatening and the seeking of emotional support undesirable and its offer impossible. Anxiety denotes the degree to which individuals worry about being rejected or abandoned by their romantic partners. High levels of anxiety manifest themselves in vigilance for signs of partner distancing as well as elevated investment in maintaining closeness by compulsively searching for support, which can overwhelm partners [40, 43] and translate into violent outbursts in addition to indifference, threats, insults, and possessiveness. Secure attachment is a protective factor for the quality of romantic relationships [44], while insecure attachment is one of the risk factors for dating violence, contributing to deficient emotional regulation [41] and conflict resolution abilities [38, 39].

In line with attachment theory, it is hoped that Dating SOS can broaden the knowledge of its participants regarding their own attachment styles and how their anxiety levels and avoidance affect their romantic relationships. In due course, this should boost action plans for emotion-regulating, including understanding aspects of the relationship that evoke negative emotions (such as exposure to violence, its perpetration, or both) as well as awareness of one’s own emotions and managing how they are expressed. It is expected that, upon receiving guidance tailored to their own attachment style and to the levels of dating violence experienced, the participants will recognize opportunities for implementing action plans more responsive to their needs and those of their partners. This in turn should reduce the use of negative conflict resolution strategies, such as distancing and excessive control, and augment the use of positive ones, such as offering to help and emotional closeness – depending on the dynamics of the relationship (violent or not) – thereby improving the quality of the romantic relationship and reducing victimization and perpetration of violence against one’s partner. Finally, one anticipates that the intervention can boost action plans and skills for seeking help or ending a relationship for those participants exposed to violence as opposed to tolerating violence, deflecting them from strategies intended to cope with insecure attachment and instead leading them to strategies related to a secure attachment style.

This article is intended describe the development process of Dating SOS, a computer tailored intervention grounded in theory for preventing dating violence and improving the romantic relationship quality of Brazilian youths. It is anticipated that the study can advance the production of knowledge in the field in three ways. First, it adopts dating violence as the focus, something little done thus far in computer tailored interventions. Second, it bases its intervention design on a collection of empirical studies of dating violence among young Brazilians, a population largely ignored in preventive actions and unstudied in this area. Third it selects, in an original way, theoretical models yet untested in CTI for dating violence prevention.

## Method

### Intervention

SOS Dating is an online intervention in which the participants receive tailored guidance based on their attachment style, their experience of having been involved in a romantic relationship with or without violence, their knowledge of dating violence, their attitudes towards dating violence, their positive and negative relationship models derived from those they spend their time and live with, the social norms regarding dating violence in their social circles, their sources of social support available for coping with violence, their self-efficacy for coping with conflicts nonviolently, and their action plans for improving the day-to-day quality of their romantic relationship and for managing conflict and protecting against violence. The tailoring also take in account the participants’ gender, sexual orientation and status of violence. Status of violence in the romantic relationship ranges from an absence of violence through episodes of violence to regular violence. In cases of regular violence or episodes of violence the direction (victimization, perpetration, bidirectional) is also considered.

The intervention comprises four individual sessions, available at http://sosnamoro.geppsvida.com.br. The content, objectives, and variables used in the customization are described on Table 1. Each session lasts approximately 15 minutes and occurs 1 week after the previous one. The feedback and participant guidance customizations were made using the *TailorBuilder* software, used in CTIs already described in literature [45, 46].

**Table 1 Tab1:** Content and objectives of the SOS Dating

	Content	Objectives
Session 1	Knowledge of attachment style	Increase knowledge of attachment styles and their impact on romantic relationships.
	Violence risk perception	Boost risk perception regarding violence experienced in a romantic relationship.
Session 2	Knowledge of violence, relationship quality, and conflict management	Identify types of dating violence: physical, psychological, sexual, and material.
		Recognize the characteristics that classify relationships as safe and gratifying as opposed to insecure and violent.
		Differentiate negative dating conflict management strategies from positive ones and its relation with attachment style.
	Positive and negative models of loving relationships	Identify models of violent loving relationships: friends, aunts and uncles, cousins, parents, grandparents, stepparents, and neighbors
		Identify models of positive loving relationships: friends, aunts and uncles, cousins, parents, grandparents, stepparents, and neighbors
	Action plans for increasing relationship quality in day-to-day coexistence	Identify damage potential in risky action plans for daily interaction: lack of communication, ignoring the partner’s needs, shutting down and ignoring one’s own needs, and not respecting the partner’s individuality.
		Construct positive action plans for daily interactions: noting the partner’s needs and providing help sensitively, sharing personal needs with the partner, asking for help, and respecting the partner’s individuality.
Session 3	Social norms regarding dating violence	Weaken the acceptance of socially disused gender stereotypes that justify violence.
	Self-efficacy in handling dating conflicts	Recognize the most challenging dating conflict situations to deal with in a non-violent way: cheating, lying, provocation, an attack by one’s partner, a bad temper, being drunk, and repeated violence.
	Action plans for non-violent dating conflicts	Identify the potential for damage in risky action plans for handling conflict: retaliation, resignation, use of alcohol or drugs, withdrawal, empathy (for victimization).
		Construct positive action plans for handing conflict: regulation of emotions, assertiveness, recognizing errors and apologizing, empathy (for perpetration), and ending the relationship.
Session 4	Attitudes toward dating violence	Strengthen the understanding that violence can be detrimental by harming the relationship, the victim, the perpetrator, and future generations.
		Weaken the perception that violence can be advantageous by granting power, self-defense, affectional gains, and financial gains.
	Social support for protecting oneself from dating violence	Recognize sources of social support for protection in the face of relationship violence.
		Actively seek social support and give clear indications that support is needed, as people may be reluctant to be invasive and help.
		Think critically and refuse social support for accepting violent relationships on the basis that they are a source of economic support, wealth, power, or that one should honor the relationship or protect the children.
	Action plans for freeing oneself from dating violence	Construct positive action plans for protecting oneself against violence: separating from the partner, seeking help, and ending the relationship.

In Session 1, called “My Relationship,” data from the attachment style and dating violence scales are used to generate tailored feedback. Based on the answers given to those scales, the participants get immediate feedback about their attachment style (secure or insecure/evasive, insecure/anxious or insecure/preoccupied), the degree of violence in the relationship (no violence, episodes of violence, or high levels of violence), and the direction of violence (victimization, perpetration, or mutual).

In Sessions 2 to 4, the participants initially answer a questionnaire focused on the dating violence determinants from the I-Change Model, including knowledge, social modeling for violent or positive intimate relations, action plans to improve the day-to-day relationship quality (Session 2 – “Improving Coexistence”), social norms, self-efficacy, action plans for conflict management (Session 3 – “Dealing with conflicts”), attitudes, social support, and action plans for self-protection in the face of violence (Session 4 – “Protecting Yourself Against Violence”). After this, they receive tailored feedback, as in Session 1.

In each session, opening and concluding narratives were used to help the participants identify with the intervention. The feedback is offered via text passages, available as narratives or lists of items, and self-monitoring exercises. They are posted to a website in a password-protected area and sent via e-mail as a PDF attachment as well. Email reminders are sent to participants 1 week after every session, if they have not completed the previous session or started the next one. All interactions between the participant and SOS Dating happen online, without the mediation of a human facilitator.

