The second study investigated the characteristics, triggers and consequences of violent conflicts in dating relationships. It was conducted via individual interviews with ten participants, six men and four women, aged 17 to 27, who had experienced dating violence, either as victims or as perpetrator-victims (i.e. bidirectional violence). The results were analyzed using deductive thematic analysis. The participants described their relationships as a mix of positive and negative experiences, with strong affective involvement but with the use of ineffective strategies of conflict management. Among those, resignation to the partner’s impositions was reported; threats, possessiveness, and casting blame to control the other’s behavior; poor emotional control (cursing and bouts of rage) accompanied by psychological, physical, and mental aggressions; attempts at reconciliation and repairing; and the withdrawal into silence and indifference toward the partner. It was reported that all these strategies resulted in new conflicts and subsequent future violence, causing great suffering to the parties involved. Furthermore, data indicated the hyperactivation of the system of attachment in the face of signals interpreted as abandonment by the partner, for example silence and distancing accompanied by anxious responses, such as emotional outbursts to make the other listen.

The third study, aimed to examine emotional intimacy and safety in the romantic relationship, keeping attachment theory as the theoretical lens. It used semi-structured individual interviews with youths between sixteen and twenty-three years of age who had dating experience. The results revealed variability among the interviewees regarding the intimacy experience, with higher levels of intimacy being connected to the exchange of social support between partners and sensitivity to each other’s needs, and threatening levels of intimacy connected to evasiveness when seeking support from the partner and negative conflict resolution strategies. The data aligned with the recommendations of attachment theory, which are that partner’s availability and accessibility are the central path for promoting emotional closeness in romantic relationships.

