#### Participants and design

An experimental design with a pre-test evaluation and three-month follow-up will be used. Youths between 15 and 29 years of age and their current partners will be invited to participate. A sample of 1220 youths, which will be randomly and evenly divided between the experimental and control groups, is expected. Participants younger than 15 and older than 29 or not currently in a dating relationship will be excluded from the intervention.

The intervention group will receive the SOS Dating intervention, while the control group will receive general information about dating violence, life skills, and sexual and reproductive rights, based on the book “Telling a night out from a trap: a Guide for the Empowerment of Teens in Intimate Relationships” (Diferenciando Baladas de Ciladas: um Guia para o Empoderamento de Adolescentes em Relacionamentos Íntimos) [48], available at http://www.geppsvida.com.br/publicacoes/cartilhas-e-guias/.

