#### Randomization

The randomization for the experimental and control group will be performed after the eligibility evaluation, the express agreement to participate in the intervention through the consent form, and the baseline evaluation. The placement into one group or the other will be performed automatically by the *TailorBuilder* software, as has been done before in other similar interventions [45, 46].

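### Tailored feedback on partner violence is e-mailed as a PDF to every intervention participant, outside the site's password, which creates an avoidable risk that a violent partner reads it

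*Protocol article*

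**What the plan says.** The Intervention section of the protocol article describes how the feedback reaches participants: "They are posted to a website in a password-protected area and sent via e-mail as a PDF attachment as well". The sentence is unconditional. It does not let the participant choose, and it does not limit the attachment by content or by the reader's violence status.

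The same section gives the content. Session 1 returns, besides attachment style, "the degree of violence in the relationship (no violence, episodes of violence, or high levels of violence), and the direction of violence", the last meaning whether the reader is victim, perpetrator or both. For Session 4, Table 1 lists this objective: "Construct positive action plans for protecting oneself against violence: separating from the partner, seeking help, and ending the relationship". It also says how contact is run: "All interactions between the participant and SOS Dating happen online, without the mediation of a human facilitator".

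Three other places bear on the point:

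- Eligibility evaluation: only people with a current romantic partner are included.
- Step 1, Needs evaluation: in the second study, interviewees who had experienced dating violence described "threats, possessiveness, and casting blame to control" the other person's behaviour.
- Participants and design: "Youths between 15 and 29 years of age and their current partners will be invited to participate".

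**The concern.** A password limits who can read the feedback on the site. A PDF in a mailbox is outside that limit: anyone who can open the mailbox, or the device on which it is open, can read the file. For most health education this would matter little. Here the file can record that the reader has been a victim or a perpetrator in the current relationship, and a later file can discuss leaving that partner. The person with most reason to react badly is the partner, and by design every participant has one.

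What is at stake is first the safety of participants, some as young as 15. Because delivery is fully automated, no facilitator is in contact who might notice that a file has been seen by the wrong person.

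A second, smaller matter is trial validity. Partners are invited into the same trial, so a forwarded or shared file could carry intervention content to a partner in the control arm.

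**Working it through.** No figure in the article describes disclosure risk, so there is nothing to reproduce. The check sets the passages side by side.

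**1. Is the attachment a stated rule or a gap?** A stated rule. The Intervention section says in the present tense that feedback goes out by e-mail as well as being posted. No other section adds an opt-in, an opt-out or a condition.

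**2. What can the file contain?** Feedback for all four sessions is delivered in the same way. Session 1 covers the degree and direction of violence in the current relationship. Session 4 covers attitudes, social support and action plans for self-protection, including separation. The most sensitive content therefore travels by the less protected channel.

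**3. Who receives it?** Everyone in the intervention arm, planned at 610 (Calculation of the sample size). All have a current partner at entry. The Background describes the programme as universal and enrols people whether or not the relationship is violent, so people in violent relationships are among the recipients.

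**4. Does the document itself give reason to expect a controlling partner?** Yes, qualitatively. The second needs study describes threats and possessiveness used to control the other. It also describes strong reactions to signals read as abandonment. A file about separation could plausibly be read as such a signal. The study does not mention monitoring of e-mail, so that step is inference.

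**5. Was the delivery channel dealt with after pre-testing?** Not as reported. In Step 6, professionals from centres for victims of domestic violence raised side-effects for participants already in violent relationships. The reported response covers visual identity, readability, message length and tailoring by violence status. E-mail delivery is not mentioned.

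**6. Does the attachment add anything that the site lacks?** Not in content. The same feedback is already in the protected area, so removing the attachment takes nothing out of the intervention.

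**7. Cross-arm exposure.** Participants and design states: "A sample of 1220 youths, which will be randomly and evenly divided between the experimental and control groups, is expected". Randomization states: "The placement into one group or the other will be performed automatically by the" TailorBuilder software. Neither section says that two partners go to the same arm. If partners were allocated independently 1:1 (an assumption), the chance that an enrolled couple is split is 2 × 0.5 × 0.5 = 0.5. The article gives neither the number of couples expected nor how much effect a shared file would carry, so the loss of contrast between arms cannot be sized. The exposure would also exist without the PDF, because feedback can be shown or copied from the website.

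**The case against.** The strongest reply is that the article condenses a fuller protocol. Consent to e-mail, privacy advice and delivery options normally sit in that document or in the consent form. Domestic-violence professionals reviewed the intervention, experts approved the revised version, and ethics approval is stated. The Background lists e-mail among the usual channels for tailored feedback, so using it is a deliberate choice. The needs-study evidence comes from ten interviewees selected for experience of violence. The mailbox would still receive SOS Dating reminders and, under the fix, a notice.

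Part of this stands. A safeguard may exist elsewhere, and a notice in the mailbox does not remove every trace of participation. But the article states the rule without condition, and the reported safety review concerns content, not channel. A neutral notice also discloses far less than a file naming the violence and plans to leave.

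Three stronger readings are tempting, and the documents do not support them:

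- *The attachment defeats the plan's own protection, so the plan contradicts itself.* The article never says what the password is for, and it names both channels together on purpose. The copy bypasses the restriction; no stated purpose is shown to be broken.
- *The attachment contaminates the control arm and shrinks the target effect by a calculable amount.* The main source of any contamination is inviting partners with no stated couple-level allocation. A forwarded PDF is tailored to someone else's attachment style and violence status, so assuming that it carries the full effect is implausible. The sample-size section also does not say whether its 10% reduction is absolute or relative.
- *The number of participants exposed can be estimated.* The Background's eight in ten is lifetime victimization or perpetration at ages 15 to 19. It is not violence in the current relationship at ages 15 to 29, and mailbox access by partners is not reported at all.

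**Conclusion.** The concern holds as an avoidable safety risk in a stated delivery rule. Every intervention participant is sent, outside the password, a file that can describe violence in the current relationship and plans for separating from the partner, with no opt-in or restriction stated. Harm requires a violent or controlling partner who can open the mailbox. The first is made plausible by the article's own interviews; the second is an assumption. The rule reaches the whole arm, but the frequency of disclosure cannot be sized from the article, and no count should be attached to it.

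Cross-arm exposure through the PDF is possible but secondary and unquantified. It depends on both partners enrolling and being placed in different arms. It should not be used to argue a specific loss of power. The case for change rests on the seriousness of the possible harm and the very low cost of avoiding it.

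**What to change.** Stop sending the feedback as an attachment by default. Send instead a neutrally worded notice, with nothing about violence or leaving a partner in the subject or body, and a link to the protected area where the same feedback already sits. Offer a PDF only as a download that the participant chooses after log-in. Amend the delivery sentence in the Intervention section accordingly. If the full protocol or consent form already contains such a choice, state it there in the article.

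The cost is a setting in the delivery software and one sentence of text. Participants must log in to re-read their feedback, which is slightly less convenient and may reduce re-reading a little. The content of the intervention does not change.

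This does not settle the handling of couples. Partners can still share what they see on the site, and a chosen download can still be forwarded. That needs a separate statement under Randomization of how two partners from one couple are allocated.
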